### Monitoring of interventions and trial progression

Participants will be asked to fill out an evaluation form concerning the interventions following the last session. These forms will assess participants’ satisfaction with the intervention as well as with the person delivering the intervention. In addition, participants will be asked to note any other comments about the interventions, allowing for spontaneously reported adverse events. As the interventions are not invasive and merely provide parents support, advice and commercially available foods with a history of safe use, no adverse events are expected and no stopping guidelines are formulated. For the same reasons, a data management committee is not needed. Principle investigators at each study site (i.e. [name]) will supervise data collection and data management. We will not perform any interim analyses as we want to avoid the risk of the results of such analyses influencing the overall results of the trial. No explicit trial conduct audit is planned; however, yearly reports on the progress of the project will be sent to the major funder of the trial (The Netherlands Organization for Scientific Research). If any major changes will occur in the study protocol (e.g., changes to outcomes or assessment periods) the ethical review boards that approved the study as well as the funder of the trial will be notified of these changes.

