### Repeated exposure and sensitive feeding

Whether a combination of repeatedly exposing infants to vegetables and encouraging sensitive feeding may lead to a better vegetable intake and liking than each of the interventions alone, has never been tested before. However, there is evidence that presentation of beneficial food choices (succeeding at the *what*) in a non-responsive manner (failing at the *how*), and the presentation of unhealthy food choices (failing at the *what*) in a responsive manner (succeeding at the *how*) may lead to overweight and eating problems in children [43, 68]. For instance, an experimental study by Galloway and colleagues showed that pressuring a child to eat, even if this pressure is mild in nature, decreases the beneficial effects of repeated exposure to the taste of vegetables [43]. This suggests that an intervention aimed at both elements may be particularly powerful.

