**Fig. 1 Fig1:**
[figure not shown]
General overview of study design

**Table 1 Tab1:** Overview of conditions and intended N per condition

Name	Description of condition	N
RVE	Repeated vegetable exposure intervention: - exposure to either green beans or cauliflower as target vegetable during the first 19 days of weaning - five phone calls to motivate parents to expose children to vegetables at child age 4–6, 8, 13 and 16 months	60
VIPP-FI	VIPP-Feeding Infants: - exposure to fruits and a sweet vegetable (carrots) during the first 19 days of weaning - five home-visits using video-feedback to promote sensitive feeding at child age 4–6, 8, 13 and 16 months	60
COMBI	Combination of RVE and VIPP-FI	60
AC	Attention control group: - exposure to fruits and a sweet vegetable (carrots) during the first 19 days of weaning - five phone calls on development of child at age 4–6, 8, 13 and 16 months	60

*Note*. *RE* Repeated exposure, *VIPP-FI* VIPP-Feeding infants, *COMBI* Repeated exposure and VIPP-Feeding infants combined, *AC* Attention-control condition

Intervention effects are assessed both during and after conclusion of the interventions by performing a pre-test at the first two days of complementary feeding (child age 4–6 months; *t*_*0*_), two assessments during the interventions (at the end of the 19-day feeding schedule (child age 5–7 months; *t*_*1*_) and when the child is 12 months old (*t*_*12*_)), a post-test at the age of 18 months (*t*_*18*_) and two follow-ups when the child is 24 (*t*_*24*_) and 36 months old (*t*_*36*_). *T*_*0*_ and *t*_*1*_ are not scheduled at a standard, fixed child age but rather within a certain age range because we wanted to allow parents to start complementary feeding when they thought their child was ready. The other measurements *are* scheduled at set child ages because the intervention sessions following the very first start of complementary feeding are scheduled at fixed time points (see *Timing of intervention sessions* below). The timeline for participants is depicted in Table 2. Participants are allowed to stop at any point during the study if they no longer want to participate. If participants decide to withdraw from the study, discontinue an intervention or are unable to complete a specific assessment, they will be asked once whether they would still be willing to complete (parts of) the intervention, the post-test and/or follow-up assessments to come.

**Table 2 Tab2:** Timeline for participants

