**Fig. 2 Fig2:**
[figure not shown]
Flowchart of the inclusion phase

Families that showed interest in our study received a phone-call from one of our trained researchers/students, explaining the study in detail. Families still expressing interest in the study at the end of the call received a detailed information brochure as well as consent forms. Both mothers and fathers were asked to sign and return the consent forms. After receiving the signed consent forms, mothers were asked to fill out an online screening questionnaire which assessed inclusion criteria. Families had to fulfil the following inclusion criteria: a) first-time mothers; b) healthy term infants (37–42 weeks of gestation); c) planning to start complementary feeding at child age of 4–6 months (families that already started complementary feeding were excluded) and d) sufficient knowledge of the Dutch language to receive advice on complementary feeding in Dutch and to be able to fill out Dutch questionnaires. Mothers with major psychiatric diagnoses (e.g., depression, schizophrenia or borderline personality disorder) were excluded, as these may affect parenting [73]. Following the study protocol of Barends and colleagues [26], families were also excluded when the first-borns were twins or in the case of medical problems in the infants that influence the ability to eat, such as food allergies, swallowing or digestion problems. Finally, for standardization purposes, mothers who were not willing to commit to the outcome of the randomization procedure were excluded, e.g. the child was assigned to a VIPP-FI group, but the mother was objecting to being video-taped. A flowchart of the inclusion phase can be found in Fig. 2.

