### Timing of intervention sessions

The five sessions of each intervention and the phone calls in the control condition are timed to take place when the infant goes through major transitions in eating (see Table 2). It was decided to give advice specifically during these major transitions to optimize the potential effectiveness of the interventions. The first two sessions are scheduled when the infant has just started eating complementary foods (approximately one and two weeks after the start). The third session is scheduled when the child reaches the age of 8 months and parents should start introducing their child to more lumpy foods to facilitate their infants’ acceptance of different food textures [76]. The fourth session is scheduled when the child is approximately 13 months and is allowed to eat the same foods as the rest of the family. Finally, the fifth session is scheduled when the child is 16 months of age to prepare parents for the potentially difficult ‘food neophobic phase’ that infants tend to reach in their second year [39, 77].

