Interveners are explicitly not allowed to give advice on *how* to feed the infant to avoid overlap with the VIPP-FI intervention. If mothers have any specific questions about feeding issues, they are referred to their youth health care center or the website of the Dutch? Nutrition Centre where parents get standard advice available for the general public.

In summary, the standardized telephone protocol for each intervention session contains the following elements:General part with standardized questions about adherence of mother and child to the vegetable guidelinesClassifying the stage of changeTesting the extent to which goals (e.g. knowledge of the topics discussed) of the previous session were achieved by asking questions and repeating information when necessary (sessions 2, 3, 4, 5)Discussing the basic information material that mothers receive per post and presenting the option to tailor the conversation by addressing the optional information and questions the mother might haveDiscussing continuation and goal setting with regard to vegetable consumption (sessions 2, 3, 4, 5)

To optimize adherence of interveners to the intervention protocol, interveners familiarize themselves with all the information in the protocol and are trained on how to approach the mothers during the telephone calls. In addition, the interveners have regular meetings to discuss the RVE intervention, exchange experiences and discuss difficulties that may arise. To allow further monitoring of adherence and achievement of the intervention goals, notes are made of each interaction with the parent. In addition, important individual details and information discussed are noted.

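### The only adverse-event route the article describes is unprompted free text on one form after the 16-month session, so an absence of reports could not be read as evidence of safety

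*Protocol article*

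**What the plan says.** The Protocol article covers safety under Monitoring of interventions and trial progression. The instrument and its timing are stated: "Participants will be asked to fill out an evaluation form concerning the interventions following the last session". The form assesses satisfaction with the intervention and with the person who delivered it. Adverse events enter through an open invitation: "participants will be asked to note any other comments about the interventions, allowing for spontaneously reported adverse events". The reason given is that the interventions are non-invasive and use commercial foods already known to be safe, so that "no adverse events are expected and no stopping guidelines are formulated".

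Timing of intervention sessions fixes the date of the form: "the fifth session is scheduled when the child is 16 months of age".

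For families who withdraw, discontinue an intervention or miss an assessment, Study design says that "they will be asked once whether they would still be willing to complete" the remaining parts of the intervention or the later assessments. It mentions neither the evaluation form nor a question about why they are stopping.

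Other contacts exist. In RVE, and in similar terms in VIPP-FI, "notes are made of each interaction with the parent", for the stated purpose of monitoring adherence and intervention goals. Control calls follow a semi-structured interview on the child's development and the mother's experience of feeding. None of these is described as an adverse-event route.

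**The concern.** The article does not leave its adverse-event method to another document. It states the method and gives a reason for it, so the method can be judged as written. Three features weaken it.

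- **Recall.** One unprompted item covers most of a year, and it asks about the interventions rather than the child's health.
- **Families who stop.** The form follows the fifth session. A family that leaves earlier because of a feeding problem has no described route to report it.
- **After 16 months.** Children are still seen at 18, 24 and 36 months, but no adverse-event item is described for those visits.

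Screening at enrolment does not fill the gap. The exclusions cover "medical problems in the infants that influence the ability to eat, such as food allergies", but Table 2 puts screening at 2–4 months, before any solid food. A reaction to a newly introduced food can appear only later.

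At stake is the safety statement in the final report. The Discussion hopes the interventions will serve large-scale prevention. A report of no adverse events that rests on an empty comment field would not support that use.

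**Working it through.** The article gives no adverse-event rate, form-return rate or drop-out by arm or over time, so there is no figure of its own to reproduce. What can be checked is the period covered, the possible number of families without a form, and whether another described measure closes the gap.

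**Look-back at the form.** Inputs: last session at 16 months (Timing of intervention sessions); age at start, mean 4.68 and range 3.98–6.38 months (Recruitment and participants).
- Mean: 16 − 4.68 = 11.32 months.
- Range: 16 − 6.38 = 9.62 to 16 − 3.98 = 12.02 months.

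**Follow-up after the form.** Last assessment at 36 months: 36 − 16 = 20 months with no described adverse-event item.

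**Families without a form.** The sample-size section needs 51 per group and recruits 60, an implied attrition of 1 − 51/60 = 15%, that is 9 per group or 36 of 240. This allowance has no time point, so it serves only as a reference value. If a fraction *d* of the 243 families that started stopped before the form (an assumption), the number without a form is 243 × *d*:
- *d* = 5%: 12
- *d* = 15%: 36
- *d* = 25%: 61

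**Does another described measure capture these events?**
- Child anthropometrics, eating-behaviour questionnaires and observed pressure to eat: all assessments to 36 months, all arms. These cover growth and feeding behaviour.
- Eating in the absence of hunger: 18, 24 and 36 months. Not an adverse-event measure.
- Question on feeding advice sought elsewhere: once, after the interventions. It asks about advice, not events.
- RVE and VIPP-FI contact notes: kept for adherence and goals.
- Control calls: development and feeding experience; no record of the answers is described.
- Request to families who stop: concerns continued participation.

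No described measure asks about a food reaction, choking, a digestion problem, a related health-care visit, or harm as the reason for stopping.

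**The case against.** The strongest reply is that this is a condensed article. Two review boards, one of them a medical ethics board, approved the trial, and a fuller protocol may hold more on safety reporting. The article does not say that the form is the exclusive route, and a light approach is a reasoned choice for advice and commercial baby food. This stands to the extent that the point must be limited to the only route described here. It does not remove the point, because the method itself is stated and is weak for the reasons given.

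Several stronger readings are tempting and are not supported:

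- *Most events are missed.* Under-reporting is likely, but nothing in the article allows the missed share to be computed.
- *Capture differs by arm.* The form is the same for everyone. COMBI has ten contacts (five calls and five visits) against five in each other arm, and notes are described for RVE and VIPP-FI but not for control calls. The notes serve adherence, so this is a possible risk and not a demonstrated difference.
- *Nothing is collected after 16 months.* Growth, eating behaviour and pressure to eat are measured to 36 months in all arms.
- *Every family that stops is lost.* They are asked once about continuing, and Fig. 2 is cited for the reasons of the 12 dyads who left before the intervention phase. Later reasons may also have been recorded, although the article does not say so.
- *The article contradicts its own expectation of no adverse events.* The background says that certain mismatches between food choice and feeding manner "may lead to overweight and eating problems in children". That includes good food offered non-responsively, which RVE does not instruct.
- *Zero reports in 51 families exclude only rates above 1 − 0.05^(1/51) = 5.7%.* This is true, but it reflects arm size. Better collection would not change it.

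**Conclusion.** The point holds as a limited one. As described, adverse events are captured through a single unprompted comment field about 11.3 months after the mean start, with no described route for families who stop before it and no adverse-event item in the following 20 months. Food reactions, choking, feeding or digestion problems and harm-related reasons for stopping may be missed, and silence on the form would not show that they did not occur.

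The number of families affected is unknown; 12 to 61 of 243 is the range under an assumed 5% to 25% stopping before 16 months. The conclusion also assumes that no fuller procedure stands in a document not shown. It does not touch the validity of the primary outcomes. It is a cheap improvement to the safety information, not a flaw in the efficacy comparison.

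**What to change.** Ask one identical, short, closed question in all four arms at each remaining contact (sessions and assessments) and at withdrawal: since the last contact, has the child had a new food reaction, choking, a feeding or digestion problem, or a related health-care visit? At withdrawal, add whether this is the reason for stopping. At the next visit, ask each family once, retrospectively, about the period already past.

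Tabulate the answers by arm for all randomised families, with the number asked at each contact, and state in the report that an empty free-text field is not taken as no adverse events.

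This is still possible for families who remain in the study. Inclusion began in May 2016 with infants of about 2–4 months. At the protocol date of 1 April 2018, some 23 months later, the oldest were about 25–27 months, so every remaining family had at least the 36-month visit ahead.

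The cost is a few minutes per contact, one added table and a notification to the two review boards, with no extra visits. More minor events will be recorded. Data on the early feeding period will depend on recall, because all 243 families had already started.

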### Dissemination policy

It is planned to publish the results of our trial in peer-reviewed journals, as well as present the results at (inter) national conferences. Also, participants will receive a report of the results of our study after completion of the study. Publication in magazines for healthcare professionals and the general public are also intended. Authorship to any publications will be granted to those who fulfil the ICMJE recommendations [109]. We will not hire any professional writers.

## Discussion

*Baby’s First Bites* will be the first trial explicitly testing the separate and combined effects of promoting the *what* and *how* of complementary feeding. By comparing three prolonged, intensive interventions, we will be able to draw firm conclusions on what is most important to focus on when promoting vegetable acceptance and children’s self-regulation of energy intake in early childhood; what food to offer, how to offer this food, or a combination of the two. Moreover, this will be the first trial to include an intervention specifically manipulating sensitive feeding practices without manipulating any other variables, evaluating its effects using both self-report and observational measures. This allows conclusions on whether this parenting practice will indeed promote healthier food preferences in children and will foster children’s ability to self-regulate their energy intake, as is often suggested in the literature.

The planned study also provides some points of discussion to be considered. First, the channels of recruitment we have chosen pose the risk that participating families are not representative of the general population, as they are partly recruited from a database of pregnant women who showed interest in information about infant nutrition. Thus, these families may be more motivated to provide a healthy eating environment for their infant than the general public. However, it should be noted that time-consuming randomized controlled trials (RCTs) like the present study will always elicit this potential selection bias, irrespective of the channels of recruitment chosen. Also, this drawback is negated somewhat by the fact that this study succeeded in including participants at all educational levels. Nevertheless, this potential selection bias should be taken into account when considering the implementation of the results of this study. Second, we chose to give parents the opportunity to start complementary feeding from the age of 4 months, thereby making sure that we followed parental preferences in starting complementary feeding. There is still some discussion in the literature about when to start complementary feeding. The general recommendation from the World Health Organization (WHO) is to exclusively breastfeed until the age of 6 months and introduce complementary foods from 6 months [1]. For the European Region, WHO [110] recommend that all infants should be exclusively breastfed from birth to about 6 months of age, and at least for the first 4 months of life, but that some infants may need complementary foods before 6 months of age, and that these should not be introduced before 4 months. The European Food and Safety Authority (EFSA) panel [111], the European Society for Paediatric Gastroenterology, Hepatology and Nutrition (ESPGHAN) [112] recommend that complementary foods including allergens are introduced between 4 and 6 months, and this has been shown to be associated with a reduced risk of food allergies [113]. Starting complementary feeding between 4 and 6 months is also in accordance with recommendations from the Dutch Nutrition Centre [114] and the Dutch youth health care centers [115] and thus reflects official Dutch guidelines and probably the daily practice of parents in the Netherlands.

Third, we chose to deliver the combined intervention by simply following the same procedures as used in each separate intervention, and the intervention was provided by two different researchers/students (one delivering RVE, and one delivering VIPP-FI). As such, it can be debated whether this really constitutes a *combined* intervention or simply *two* interventions. Also, from the families’ point of view, receiving advice from two different persons might not be ideal. An alternative approach would have been to incorporate all information of both interventions in the home visits. However, we decided against this as the VIPP-FI home visits already took up 60 to 90 min. Including the information of the RVE intervention in this session would result in too much information for the mother to properly process in one sitting, increasing the risk that the effects of the intervention would diminish. Fourth, considering the time-consuming nature of this study for families, there will be a considerable risk of drop-out during the study. This risk is even higher in the selected sample of first-time mothers, as it is likely that many families will expand their family during the study period, making the time they have available for participating in this study more limited. We plan to accommodate families as much as possible to make sure that they will be able to finish the study, for instance by offering assistance where necessary (e.g., filling out questionnaires together or sending personal reminders) and by being flexible in planning the home-visits.

Finally, if the proposed RCT will prove the interventions effective, the labor intensiveness of the tested interventions may pose problems for their implementation to the general public. Although this is not so much a limitation of the current study, it is a drawback for implementing its results, as it will be necessary to translate the interventions to scalable prevention programs before the interventions can be implemented for a larger group.

In conclusion, the planned trial has the potential to provide valid evidence on the question how parents may promote healthy eating habits from the very first start of eating solid foods. If proven effective, these interventions could be useful to large scale effective prevention of childhood obesity.

